
### Adverse effects

Adverse effects are defined as negative outcomes associated with participation in the current trial. Possible adverse effects due to study participation might be injury resulting from increased physical activity. The occurrence of any adverse effects will be tracked and evaluated via the semi-structured interview.

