### Evaluation design

A one-arm, multicenter mHealth interventional study will be performed. Participants complete all assessments in the app with the same assessment rhythm irrespective of when participants enroll in the study. Upon registration, participants can complete questions on socio-demographic variables, psycho-social determinants (e.g., intention, self-efficacy), physical activity, nutrition and mindfulness as well as health-related outcomes (e.g., back pain). Data will be collected across a 100-day period at four assessment points: baseline (booking date + 0), interim after 4 weeks (booking date + 28) and 8 weeks (booking date + 56) and post-intervention (booking date + 99). Additionally, 11 weekly assessments will be scheduled (booking date + 7, + 14, + 21, + 35, + 42, + 49, + 63, + 70, + 77, + 84, + 91). Participants will receive reminder emails for the baseline and post assessment four days after the respective assessment date (i.e., baseline reminder booking date + 4 days, post assessment booking date + 104 days). Reminders for the remaining assessments are incorporated into the app (via “open tasks”, see Description of the intervention for further information). Outcome data will be the same for all participants, whether they continue or discontinue/deviate from the intervention protocol. One week after the completion of the intervention, a structured interview is scheduled with volunteers to gain insights in participants’ experiences with the app (e.g., practicability, operability, acceptability). Due to economic reasons, the total set of items varies per assessment point. The Fig. 3 presents an overview of the enrolment schedule, the intervention, worksheets and assessments.

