#### Semi-structured interview

Upon completion of the post-assessment (100-days post baseline) participants are invited to voluntarily take part in an interview (approximate duration 30–60 min). Main topics of the interview are: experiences with app in general, experiences with operability of app (e.g., setup), experiences with practicability (e.g., in the work context), app user behavior, opinion about personal relevance and effects of the app on health behavior. Reasons for dropout will be evaluated for participants who withdrew during the intervention period. An overview of the main interview questions is presented in Table 2.

**Table 2 Tab2:** Overview of semi-structured interview questions about participants’ experiences with the Habit Coach app (process evaluation)

Topic	Question
General experiences with app	What are your experiences with the app? Please elaborate.
Experiences with operability of app (e.g., setup)	How do you perceive the operability (e.g., setup of menu) and features of the app?
Experiences with practicability (e.g., work context)	How practicable do you perceive the app during your working routine?
App user behavior	How, how often, when and where do you preferably use the app?
Opinion about personal relevance	As how personally important and relevant do you perceive the app?
Effects of app on health behavior	What effect does the app have on your health behavior? Have you made any changes in your behaviors due to using the app? Please also think about any spontaneous negative events or unintended effects of the app. Please elaborate.

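### The only stated route for recording adverse effects is a voluntary interview after the programme, so events among non-volunteers go unrecorded and no usable incidence for the enrolled cohort can be given

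*Protocol article*

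**What the plan says.** The Adverse effects section names a foreseeable harm, "Possible adverse effects due to study participation might be injury resulting from increased physical activity", and one way of recording it: "The occurrence of any adverse effects will be tracked and evaluated via the semi-structured interview".

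Two other sections describe the interview. Evaluation design says: "One week after the completion of the intervention, a structured interview is scheduled with volunteers". The Semi-structured interview section says that, on completing the post-assessment, "participants are invited to voluntarily take part in an interview (approximate duration 30–60 min"). In the overview of main questions (Table 2), harm appears once, as an open prompt inside the question about effects on health behaviour: "Please also think about any spontaneous negative events or unintended effects of the app".

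The Semi-structured interview section also says: "Reasons for dropout will be evaluated for participants who withdrew during the intervention period". It does not say how, when or by whom these people are contacted.

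Evaluation design schedules 15 in-app assessments for every participant: baseline, 11 weekly, two interim and post. The content listed for them under Measurement instruments, the weekly assessments and Process evaluation includes no adverse-effect or injury item. The nearest items are back health and back pain (Health status), which are outcomes compared from baseline to post. The Data management section states that no monitoring committee was assigned.

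**The concern.** The plan sets out to track any adverse effect, but asks only people who finish, volunteer and give up to an hour of their time. They are asked once, about a period of up to 107 days (100 days plus one week, roughly 15 weeks). Those interviewed are self-selected, and their willingness to be interviewed may be related to how the programme went for them.

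What is at stake is the safety statement in the final report. A report that interviewees mentioned no harm would say little about the enrolled cohort, and a reader could easily take it to mean more. An analysis plan cannot repair this later, because it cannot analyse events that were never collected.

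**Working it through.** The protocol gives no adverse-effect rate, interview uptake or safety precision, so there is no figure of its own to reproduce. The first step sets the passages together; the rest illustrates scale.

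**1. Who can be recorded.** Adverse effects section: the interview is the route. Evaluation design and Semi-structured interview: the interview is voluntary and follows the post-assessment. Listed questionnaire content: no adverse-effect item. A completer who declines the interview therefore has no stated route. A participant who withdrew has the drop-out evaluation, whose method is not given.

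**2. Number reaching the invitation.** Inputs from Statistical power: N = 228, allowing for 30% attrition. Completers = 228 × (1 − 0.30) = 159.6, about 160.

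**3. Number asked, and what zero reports would show.** Uptake u is an assumption. Interviewed n = 159.6 × u, rounded. Coverage = n / 228. Exact one-sided 95% upper limit with zero events = 1 − 0.05^(1/n).

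| Assumed uptake | Interviewed | Share of 228 | Upper limit, zero events |
|---|---|---|---|
| 10% | 16 | 7% | 17.1% |
| 20% | 32 | 14% | 8.9% |
| 30% | 48 | 21% | 6.1% |
| 50% | 80 | 35% | 3.7% |

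These limits carry over to the cohort only if volunteering is unrelated to having been harmed. For comparison, if all 228 were asked and none reported an event, the limit would be 1 − 0.05^(1/228) = 1.3%.

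**4. Expected number of events surfaced.** Assume a true rate of 5%, that is 228 × 0.05 = 11.4 events, with volunteering unrelated to harm. Interviews would then surface n × 0.05 = 0.8, 1.6, 2.4 and 4.0 events at the four uptakes.

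**5. Incidence without that independence assumption.** Suppose 5% of interviewees report an event and uptake is 50%, so the covered fraction is s = 0.70 × 0.50 = 0.35. With the others unrestricted, incidence in all enrolled lies between 0.05 × 0.35 = 1.8% and 0.05 × 0.35 + 0.65 = 67%. Lower uptake widens this; at 10% it is 0.35% to 93%.

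**6. Most favourable reading of the drop-out sentence.** Suppose every one of the 228 − 160 = 68 non-completers is reached and asked about harm. Completers who were not interviewed still number 160 − 80 = 80 at 50% uptake and 160 − 16 = 144 at 10%, that is 35% to 63% of 228. The gap narrows but does not close.

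**The case against.** A reader might infer that injuries causing drop-out are the ones most surely lost, or that most injuries will be missed. The documents do not support either as stated. The Semi-structured interview section provides for reasons for drop-out to be evaluated among those who withdrew, so an injury that led to withdrawal has a planned route, although an undescribed one. How large a share is missed depends on an interview uptake that the protocol does not give.

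Further points on the other side:

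- The plan promises no incidence and has no safety hypothesis; the Objectives concern habit formation and its predictors. This stands. The habit analyses are untouched, and the weakness lies in what can be said about harm.
- Table 2 is only an overview of a semi-structured interview, so probes about injury may well be used. This also stands. The point does not rest on the wording of the prompt.
- The risk context is mild. People with musculoskeletal disease, osteoporosis or arthrosis are excluded, the exercises given as examples are stretching and walking, and a coach can be contacted. This bears on how urgent the matter is. Coach contact is not described as adverse-effect recording, and changes in back pain or health status cannot be read as event counts.
- In-app items also lose people who stop answering. That is true, and it limits what the remedy can deliver.

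**Conclusion.** The point holds in this form: the one stated route for adverse effects is a voluntary interview after the programme, drop-out reasons are to be evaluated by no stated method, and no in-app assessment is described as carrying an adverse-effect item. Events among completers who do not volunteer will go unrecorded. The result would be a statement about a self-selected group, with the number interviewed as its only denominator.

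The size is an illustration. It takes 228 as the number enrolled, the stated 30% attrition as the loss before the post-assessment, and an assumed uptake of 10% to 50%. The conclusion that no usable incidence can be given for the enrolled cohort does not depend on where in that range uptake falls. This is a worthwhile, low-cost improvement to safety reporting and does not threaten the primary endpoint.

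**What to change.** Add one yes/no item with free text to the interim and post in-app assessments, and preferably to the weekly ones. It should ask whether, since the last questionnaire, the participant has had an injury or other negative effect that they relate to the exercises or the app. State how participants who withdrew will be contacted for their reasons, and put the same item in that contact.

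Report counts with the number of respondents and the person-weeks answered as denominators, and show non-response at each assessment. Do not present the result as incidence over all enrolled without that qualification. Keep the interview for detail on reported events.

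The cost is one extra item per assessment and a short amendment. The protocol itself lists the number of assessments as an attrition risk, so the item should stay short; if burden decides the matter, interim and post alone are a reasonable minimum, at the price of longer recall. Drop-outs who stop answering would be reached only through the drop-out contact.

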### Dissemination

The results of this trial will be published in international peer-reviewed journals and presented on national and international conferences. Additionally, the trial has been pre-registered and is publicly available by the German Clinical Trials Register and the World Health Organization. All relevant data (in accordance with the informed consent form) from this study will be made available upon study completion.

## Discussion

### Overview and implications

Irregular and long work schedules often prevent health care professionals from regular engagement in health promoting behaviors [7]. Promoting health enhancing behaviors in health care professionals is therefore of upmost importance. This trial addressed this call by taking into account the adverse working conditions of health care professionals, as well as acknowledging that behavior change is not solely a product of deliberative psychological but also of non-conscious processes. Through a mHealth intervention fostering healthy habit formation for physical activity, nutrition and mindfulness practices, and easily integrable theory- and evidence-based strategies facilitative of habit formation, shortcomings of previous research are overcome. We examine whether the mHealth intervention can increase participants’ habit strength for physical activity, nutrition and mindfulness behaviors. In addition, it will be examined whether potential changes in habit strength are predicted by changes in psychosocial variables. Through the weekly assessments we are able to seek insights into participants’ weekly struggles to adopt a healthy way of living.

### Strengths, challenges and limitations

Strengths. The mHealth intervention is theory driven and provides support during the entire behavior change process, starting with a motivational (i.e., goal setting), over a volitional (i.e., action planning) to habit formation and behavioral maintenance phase. Although mHealth interventions intended to increase physical activity and eating behaviors have shown positive effects, these effects often times were small and highly variable, caused by insufficient description of theoretical foundations and behavior change techniques used. The present study focuses specifically on mechanisms of action and respective behavior change techniques in order to predict change in behavior and make intervention design and evaluation more transparent and replicable. Furthermore, by allowing health care professionals to integrate the within-app mini interventions into their daily (work) routine, it is intended to tackle commonly reported problems of implementing programs such as massive disruption of the working day and attrition based on problems to fit interventions into daily routines outside the work context.

Limitations. The study design is not without limitations. First, we are not able to collect participants for a control group, as the resources for this study are limited. Consequently, it is not possible to evaluate the effectiveness of the mHealth app. Furthermore, due to the uncontrolled design it is not possible to help close the knowledge gap pertaining to the question, as to whether traditional context-dependent repetition is necessary for habit formation or if it represents the most promising or reliable ingredient of habit formation interventions. Future studies are warranted to compare and evaluate habit formation interventions against non-habit based programs. Second, the mHealth evaluation is also limited given that no follow-up period is included. Whether habits indeed last over time and so facilitate behavioral adherence, cannot be confirmed without (or even with short) follow up periods [29].Third, in order to test our hypotheses participants will need to take part in many assessments, which might result in high attrition rates. We try to prevent dropouts by sending email reminders and keeping incomplete questionnaires available on the home screen under “open tasks”. Lastly, as the researcher(s) who analyze the data will also be involved in the data-collection process and in the study design, blinding of the analyst is not feasible. In the next step, the summative evaluation of the Habit coach app against a control group in a randomized controlled trial is warranted.

In sum, this trial addresses health care professionals’ adverse working and health conditions and acknowledges that health behavior change is a results of deliberative as well as non-deliberative psychological processes. Through a mobile app fostering healthy habit formation in the areas of physical activity, nutrition and mindfulness behaviors and theory-based strategies to support habit formation, shortcomings of previous research are overcome. The analyses and evaluation of the app will provide insights in the habit formation process supported by the app and will contribute to the mHealth literature in both theoretical and practical aspects.

## Data Availability

Not applicable.
